Although randomization at the physician/patient level is sample-size efficient, we chose a cluster randomization by clinic because contamination is a major concern. If we randomize at the physician level, physicians in the same clinic who are assigned to different treatment arms might communicate regarding the CHICA system in terms of its operation and consequences, which could contaminate the control arm. If we randomize at the patient level, the on and off usage of the CHICA might confuse the physician and lead some to think that CHICA is malfunctioning. Anecdotally, this has been our experience with the asthma and maternal depression studies we have conducted. We have found previously that randomization at the patient level can lead to irritation and inconvenience for both physicians and clinic staff. The limitation of randomization at the clinic level is inflated sample size and potential bias caused by unknown characteristics that are differentially distributed in the four clinics and related to the outcome. Characteristics of this nature could include awareness of ASDs by physicians, socio-economic status of patients and so on. To our knowledge however, there is no reported significance and scale of the effect of these factors. After weighing the limitation and advantage of each option, we decide to allocate two clinics to each of the study arms. We will adjust for intra-cluster correlation and potential confounders in the analysis.

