### **D.4 Sample Size (Aims 2 and 3)**

#### D.4.1. Sample Size Calculation for Aim 2

The primary outcome of interest for aim 2 is the proportion of children at the 18 or 24-month visits that will be screened for ASD using the M-CHAT in the intervention group and any ASD specific screening tool in the control group. Dosreis and colleagues found that while 82% of pediatricians reported screening for general developmental delays, only 8% screened for ASD. Though we do not anticipate much variability in this rate at our study clinics, we will use four different rates, 6%, 8%, 10% and 12%, at baseline to estimate intra-clinic correlation. This translates to an intra-class correlation coefficient 0.0041. However, for a conservative estimation of sample size, we will use intra-class correlation 0.0082, twice that of the correlation we estimated.

To be conservative, we will assume 10% of the children are screened for ASD under standard practice in our clinic sites. Based on pilot data involving a different universal screening tool in the pediatric population (i.e., the Ages and Stages Questionnaire), we expect at least 50% of the children at the 18 or 24-month visits will be screened in the intervention clinics. However, we will use a more conservative estimate, that is, 40% of the children will be screened using the M-CHAT.

Using a chi-square test and setting alpha at 0.05, the probability of detecting a statistically significant difference in the proportion of children screened at the 18 or 24-month visits between the intervention and the control group is 90% with an effective sample size of 49 per group. Hence, the total effective sample size ( $n^*$ ) is 98. The unit of randomization is the practice or clinic, but the unit of analysis is the individual patients. Since patients are nested within practice, responses from the patients within practice are likely to be correlated. This intra-cluster correlation must be taken into account in the calculation of sample size and in the analyses. We computed the number of patients per clinic,  $m$ , required for the study, using the following equation:

$$m = \frac{1 - \rho}{\frac{k}{n^*} - \rho}$$

where  $\rho$  = intra-practice correlation,  $k$  = number of clinics,  $mk$  = total sample size,  $n^*$  = total effective sample size =  $mk/DE$ , and  $DE$  = design effect =  $1 + \rho(m-1)$ 

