### **D.5 Data Analysis (Aims 2 and 3)**

For each of the two aims, baseline clinical and demographic data will be compared between the intervention and the control groups. Categorical variables will be examined using chi-square tests and continuous measures with Student's t-tests. The statistical analysis of the data will be performed using the SAS.

#### D.5.1. Data Analysis for Aim 2

The primary variable for aim 2 is whether a child at the 18 or 24-month visits was screened for ASD using the M-CHAT in the intervention group and any ASD specific screening tool in the control group. For this dichotomous outcome, we will use a non-linear mixed-effects model and will adjust for potential confounders (fixed effects) and clinic effects (random effects). To be specific, if  $Y_{ik}$  is a binary variable indicating whether the  $k^{\text{th}}$  patient in the  $i^{\text{th}}$  clinic was screened, we have

$$\log it(Y_{ik} = 1) = \alpha_i + \mathbf{X}_{ik}\boldsymbol{\beta}, \text{ where } \alpha_i \sim N(0, \varepsilon^2).$$

The random component  $\alpha_i$  correlates outcomes of patients cared by the same clinic. Physicians would not be considered as a nesting factor since the same patients at different visits may not be seen by the same physician. The vector  $\mathbf{X}_{ik}$  represents fixed covariates and  $\boldsymbol{\beta}$  represents the corresponding coefficients. The fixed covariates will include critical covariates such as treatment group, gender, and other patient and clinic level characteristics. We will also examine potential interaction terms among the covariates, particularly interactions between treatment arm and other covariates. If there is a significant treatment difference, we will report the 95% confidence interval of the treatment difference after adjusting for all confounding factors. The model will be fitted by the SAS procedure NLMIXED.

All secondary dichotomous outcomes, for example, whether a child under the age of 5 undergoes surveillance for ASDs, whether ASD surveillance led to diagnosis of ASD with an ASD specific screening tool and whether a child was referred for comprehensive ASD evaluation will also be analyzed using the same model as described above.

### D.5.2. Data Analysis for Aim 3

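### The Aim 2 primary test, a maximum-likelihood random-intercept logistic model on four clinics with clinic-level covariates, does not reliably hold its 5% error rate

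*Protocol*

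**What the plan says.** Protocol section D assigns four clinics, two to each arm, and promises an analysis that allows for clustering: "We will adjust for intra-cluster correlation and potential confounders in the analysis". D.5.1 gives the primary model: a logistic regression for whether each child was screened, with a normally distributed random intercept for clinic. Its fixed covariates are described as "such as treatment group, gender, and other patient and clinic level characteristics". On fitting it says: "The model will be fitted by the SAS procedure NLMIXED". The same model is to serve all secondary dichotomous outcomes of Aim 2. No reference distribution, degrees of freedom or limit on clinic-level covariates is given.

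The Aim 2 sample size section (D.4.1) works differently: "Using a chi-square test and setting alpha at 0.05", the power "is 90% with an effective sample size of 49 per group", inflated by a design effect to 31 children per clinic. It adds that at least 1000 children a year, or 3000 over three years, attend the four clinics for these visits.

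**The concern.** Treatment is constant within a clinic, so all information on its error comes from differences between clinics in the same arm. Four clinics minus two arm means leave 2 df. NLMIXED fits by maximum likelihood, which in effect divides the between-clinic sum of squares by 4 where an unbiased estimate divides by 2. With so few clinics the estimated clinic variance is often zero, and the test then treats the children as independent.

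Clinic-level covariates draw on the same 2 df. One leaves 1 df. Two, with the intercept and treatment, fit the four clinic means exactly; the clinic variance goes to zero and the treatment standard error ignores clustering.

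At stake are the p-value and confidence interval for the primary outcome, and those of the secondary dichotomous outcomes.

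**Working it through.** **Inputs.** From D.4.1: alpha 0.05 (taken as two-sided); control rate, "we will assume 10% of the children are screened for ASD under standard practice in our clinic sites"; intervention rate, "40% of the children will be screened using the M-CHAT"; the estimated ICC, "This translates to an intra-class correlation coefficient 0.0041", doubled to 0.0082 for planning; 31 children per clinic required; 1000 to 3000 children available, so 1000/4 = 250 to 3000/4 = 750 per clinic. From section D: four clinics, two per arm.

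**The plan's own figures.** For 10% v 40% at 90% power, the two-proportion formula gives 42 per group without a continuity correction and 49 with it, so 49 is reproduced. With k = 4, n* = 98 and ρ = 0.0082:

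m = (1 − 0.0082)/(4/98 − 0.0082) = 0.9918/0.03262 = 30.4, rounded up to 31.

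The arithmetic is right, but it treats the clinic variance as known.

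**Limiting case.** When clinic variance dominates, the variance estimate is half its proper size, so the Wald statistic is √2 times a t variable on 2 df.
- Normal reference: P(|t₂| > 1.96/√2) = 30%.
- t on 3 df: P(|t₂| > 3.182/√2) = 15%.

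**Simulated type I error.** Both arms at 10%, two clinics per arm, no clinic-level covariate, ICC 0.0082. The logistic fits are maximum likelihood by adaptive quadrature, about 1500 trials at 31 per clinic and 1000 at the larger sizes. The second figure in each pair is a normal approximation on four clinic summaries with 400,000 trials. As the protocol gives no reference distribution, both a normal and a t on 3 df (clinics minus one) are shown as assumptions.

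| Children per clinic | Design effect 1 + (m−1)ρ | Normal reference | t on 3 df | t-test on four clinic rates, 2 df |
|---|---|---|---|---|
| 31 | 1.25 | 5.8% / 7.2% | 0.0% / 0.4% | 4.1% / 5.0% |
| 250 | 3.04 | 18.5% / 18.5% | 4.1% / 4.2% | 4.5% / 5.0% |
| 750 | 7.14 | 25.2% / 25.7% | 10.1% / 9.9% | 4.7% / 5.0% |

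The Monte Carlo standard error of the 5.8% is about 0.6 percentage points. The logistic fit put the clinic variance at zero in 81%, 47% and 27% of trials at the three sizes. At the lower ICC of 0.0041 and 750 per clinic, the error is 21.6% (normal) and 5.6% (t on 3 df).

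**Clinic-level covariates.** With one, at 750 per clinic and ICC 0.0082, the error is 34.7% (normal) and 17.5% (t on 3 df). With two, the test is an unclustered one. With a normal reference its error is 2[1 − Φ(1.96/√DE)]: 8%, 26% and 46% for design effects 1.25, 3.04 and 7.14.

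**Power of the 2-df clinic-level t-test**, 10% v 40%, ICC 0.0082: about 53% at 31 per clinic, 89% at 250 and 94% at 750. At ICC 0.0041 it is about 56%, 96% and 99%.

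**The case against.** The strongest reply is that the protocol fixes the model and the procedure but not the reference distribution or df, which a statistical analysis plan may set. At the required 31 per clinic the normal-reference error is close to nominal. The large liberal figures need both a normal reference and the 250 to 750 per clinic that the protocol gives as availability, not as its requirement. With the same maximum-likelihood fit referred to 2 df and no clinic covariate, the error is about 0.01%, 0.8% and 3.9% at 31, 250 and 750 (ICC 0.0082): conservative, not inflated.

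Much of this stands. A reader might infer that the planned test is liberal throughout, or at the stated sample size. The documents do not support that: the direction depends on two things D.5.1 leaves open. A reader might also take 26% and 46% as the expected error. Those figures assume exactly two clinic-level covariates, and the protocol names none and sets no number. Nor is the statement in section D about adjusting for clustering an error; it is an intention that the specified model does not reliably deliver.

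It does not remove the point. Neither a normal reference nor t on 3 df holds 5% across the protocol's own range of clinic sizes, and cells near 5% are coincidences of size and ICC. Setting 2 df swaps inflation for marked conservatism. No choice of df repairs a model saturated by clinic covariates. The use of more than 31 per clinic is plausible, since D.2.3 seeks a consent waiver and D.2.4 describes automatic data capture in all clinics.

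**Conclusion.** The concern holds in this form: the specified primary test cannot be relied on for a 5% error rate or a 95% interval. At ICC 0.0082 and a 10% rate, its type I error runs from about 0% to 25% without clinic covariates, depending on children per clinic and on whether a normal or a 3-df reference is used; both references are assumptions. One clinic covariate raises it further at large clinic sizes, and two remove the allowance for clustering altogether.

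If the effect is as large as 10% v 40%, the primary conclusion may well survive. The stated precision would not, and the secondary outcomes analysed by the same model have no assumed effect of that size. The benchmark 2-df t-test holds 5% on the assumption of roughly normal clinic summaries with equal variance in the two arms.

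**What to change.** Reword D.5.1 so that the primary test is a two-stage clinic-level analysis. First fit a patient-level logistic regression on patient covariates, without treatment. Then compare the four adjusted clinic summaries between arms with a t-test and confidence interval on 2 df. Take clinic-level characteristics out of the model and report them descriptively. Apply the same rule to the secondary dichotomous outcomes.

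A mixed model fitted by restricted pseudo-likelihood with treatment df set to 2 should not be offered as equivalent. With the clinic variance bounded at zero, its type I error in the normal approximation is about 0.01%, 0.5% and 2.2% at 31, 250 and 750 per clinic.

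The cost is more than rewording. The interval will be wider, and the 90% power in D.4.1 must be restated for the 2-df test: about 53% at 31 per clinic, 89% at 250 and 94% at 750 (10% v 40%, ICC 0.0082). Power near the stated level therefore means analysing the children already seen at the 18- or 24-month visits, 250 to 750 per clinic, in place of 31. No additional clinics are needed under these assumptions. The result is sensitive to the ICC: at an assumed 0.03, power is only about 59% at 250 and 61% at 750.

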Using 4 clinics and assuming intra-class correlation of 0.0082, we need to recruit 31 children per clinic. We anticipate that drop-out is not a major problem and unlikely to be more than 10% for the primary outcome. We will account for this factor by oversampling patients by 10%. According to our previous experience and data from the four clinics included in this study, at least 1000 patients present to these four clinic sites for 18 or 24-month visits each year, leading to 3000 patients if the study runs for 3 years.

#### D.4.1. Sample Size Calculation for Aim 3

For aim 3, children between the ages of 18 months through 5 years with newly diagnosed ASD will be included as potential participants. The primary outcome of interest for this aim is the number of activities/involvements (listed in Figure 9) that a child diagnosed with an ASD is receiving. Although better outcomes are expected in the intervention group, no preliminary data are available to support this hypothesis. Hence, the primary purpose of this study is to generate preliminary data on this outcome in order to design a large scale study. Even though the screening rate could be as low as 8% in the intervention group and 40% in the intervention group, the vast majority of children should still receive a diagnosis of ASD by age 5 even without standardized screening at the 18 or 24-month visits. It is likely that we will have at least 80% of the children with a diagnosis of ASD receiving care for that diagnosis by age 5. Though we do not know how many children with newly diagnosed ASD will be available in each of the four clinics, we anticipate more than 20 children in each of the two treatment groups assuming a prevalence of 1 in 150, successful identification of 80% of children with diagnosis ASD, and recruiting about 4000 per group. In 2007, the four study clinics saw 8,528 patients between ages of 0 and 3 years and 3,065 patients between the ages of 4 and 5. Hence, we do not anticipate any problem in having 4000 children per group for this study. We base the sample size justification on estimation and not hypothesis testing. A sample size of 20 per group can be considered adequate for a pilot study given that a sample size as low as 12 in each group provides adequate power for precision in estimating the difference between means in clinical trials in the sense that the gains in precision are less pronounced as sample size exceeds 12.

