Aim 3 involves the collection of pilot data and hence we may not have adequate power to detect a difference between the intervention and control groups. We will collect data on the primary outcome, the number of activities/involvements (listed in Figure 9) that a child diagnosed with an ASD is receiving and on secondary multiple patient improvement outcomes at baseline, 6 and 12 months. We will model the longitudinal data on primary outcome measured at baseline, 6 and 12 months and the change in secondary outcomes. For example, change in problem behaviors, parent stress and satisfaction at 6 and 12 months from baseline. The nature of our data is complex, a three-level data structure. The three levels are occasion of measurements, patients and clinics. Patients (level 2) are nested within clinic (level 3) and repeated measurements (level 1) are nested within patient. The model for observation  $Y_{ijk}$ , that is, observation for the  $k^{\text{th}}$  patient at time  $j$  and  $i^{\text{th}}$  clinic, is given by

$$Y_{ijk} = \alpha_{0i} + \delta_{0k} + \mathbf{X}'\boldsymbol{\beta} + \varepsilon_{ijk}$$

where the independent components

$$\alpha_{0i} \text{ distributed as } N(0, \sigma_{(3)}^2) \quad \delta_{0k} \text{ distributed as } N(0, \sigma_{(2)}^2) \text{ and} \\ \varepsilon_{ijk} \text{ distributed as } N(0, \sigma^2)$$

The random component  $\alpha_{0i}$  correlates observations within the same clinic and the random component  $\delta_{0k}$  correlates repeated observations from the same patient. The vector  $\mathbf{X}$  represents fixed covariates and  $\boldsymbol{\beta}$  represents the corresponding coefficients. We will use proc mixed available in SAS to fit this model. The fixed covariates will include treatment group, time, gender, race, age, baseline value of the response variable and other potential clinical outcomes. Baseline value of the primary outcome will not be a covariate in modeling primary outcome since the response vector ( $Y_{ijk}$ ) will include the baseline outcome. We will first test for the interaction effect between time and treatment group. If there is no interaction effect, we will evaluate the overall treatment difference. Otherwise, treatment difference will be assessed at each time point. If there is a significant difference, we will report the 95% confidence interval after adjusting for all confounding factors.

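### When its interaction pre-test is non-significant, the Aim 3 primary analysis averages baseline into the treatment difference, and both aims report a 95% CI only on significance

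*Protocol*

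**What the plan says.** Protocol D.5.2 sets out the Aim 3 primary model: "We will model the longitudinal data on primary outcome measured at baseline, 6 and 12 months". It is a linear mixed model with random intercepts for clinic and patient; the patient term "correlates repeated observations from the same patient". For the secondary outcomes the baseline value is a covariate. For the primary outcome it is not: "Baseline value of the primary outcome will not be a covariate in modeling primary outcome since the response vector" includes it.

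The time-by-group interaction is tested first. Then: "If there is no interaction effect, we will evaluate the overall treatment difference". The alternative is: "Otherwise, treatment difference will be assessed at each time point". Nothing restricts the overall difference to the follow-up occasions or sets the baseline means equal across arms.

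On reporting, D.5.2 says: "If there is a significant difference, we will report the 95% confidence interval after adjusting for all confounding factors". D.5.1 has the same condition for Aim 2: "If there is a significant treatment difference, we will report the 95% confidence interval of the treatment difference".

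The Aim 3 sample size section in D.4 gives the purpose as preliminary data for designing a larger study, and adds: "We base the sample size justification on estimation and not hypothesis testing". D.5.2 itself concedes that power may be inadequate.

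The schedule is not consistent. D.3.4 Data Collection has the activity checklist completed at 6 and 12 months after diagnosis and names baseline only for the Table 1 patient outcomes. D.5.2 places a baseline value of the checklist count in the response.

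**The concern.** Once baseline is one of the responses, an effect that begins after baseline appears as a difference between arms that changes over time, which is the interaction. The plan turns to a single overall difference only when it has failed to detect that change, and that difference then includes an occasion at which little or no effect would be expected. The main product of Aim 3 is an estimate for planning the next trial, and on this branch it is pulled toward the baseline difference.

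The interval rule is a second, separate problem. A pilot of about 20 children per group will often be non-significant. Its interval is then what a planner most needs, and the protocol does not promise one.

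**Working it through.** **The plan's own figure.** D.4 expects more than 20 children per group from 4000 children, a prevalence of 1 in 150 and 80% identification: 4000 × (1/150) × 0.80 = 21.3. This reproduces. The calculations below use 20 per group.

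**What the overall difference estimates.** Let d0, d6 and d12 be the differences between arms at baseline, 6 and 12 months. With a random patient intercept, time as a factor, no interaction term and complete data, each occasion has equal weight:

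overall = (d0 + d6 + d12)/3 = (1/3)·d0 + (2/3)·(d6 + d12)/2.

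With d0 = 0 this is two thirds of the mean follow-up effect, whatever the time pattern and the variances:

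| Profile (baseline, 6, 12 months) | Three-occasion average | Mean of 6 and 12 months | Ratio |
|---|---|---|---|
| 0, d, d | 0.67d | 1.00d | 0.67 |
| 0, 0.5d, d | 0.50d | 0.75d | 0.67 |
| 0, 0, d | 0.33d | 0.50d | 0.67 |
| 0.3d, 1.3d, 1.3d (persisting gap) | 0.97d | 1.30d | 0.74 |
| −0.3d, 0.7d, 0.7d (persisting gap) | 0.37d | 0.70d | 0.52 |

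Missing follow-up gives baseline more weight. For a constant effect and correlation 0.2 to 0.8, the coefficient is about 0.65d with 10% missing at 12 months, and 0.61d to 0.62d with 10% missing at 6 months and 20% at 12 months.

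**How often the pre-test sends the analysis down this branch.** The protocol gives no effect size, SD or within-child correlation for Aim 3. The following are therefore assumptions: constant effect d of 0.3, 0.5 or 0.8 SD at both follow-ups, correlation ρ from 0.3 to 0.7, two-sided 5% level, clinic variance ignored. With n = 20 per group the interaction F test has 2 and 2(2n − 2) = 76 degrees of freedom, and noncentrality

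λ = (n/2)·Σ(dj − d̄)²/(1 − ρ) = (n/2)·(2/3)d²/(1 − ρ).

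At d = 0.5 and ρ = 0.5: λ = 10 × (2/3) × 0.25/0.5 = 3.33, and power is 0.34.

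| d (SD) | Interaction power, ρ = 0.3 / 0.5 / 0.7 | Interaction missed, ρ from 0.7 to 0.3 |
|---|---|---|
| 0.3 | 0.12 / 0.15 / 0.22 | 78-88% |
| 0.5 | 0.25 / 0.34 / 0.53 | 47-75% |
| 0.8 | 0.57 / 0.73 / 0.92 | 8-43% |

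Simulating the two-stage rule at ρ = 0.5 (20,000 runs per effect size), the interaction was missed in 85%, 65% and 27% of runs. The mean overall estimate in those runs was 0.66d to 0.67d, so conditioning on the failed pre-test does not remove the dilution.

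**Cost in precision.** At d = 0.5 and ρ = 0.5, the variances of the group contrast, in SD² units, are:

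- three-occasion average: (2/n)(1 + 2ρ)/3 = 0.0667, SE 0.258, expected estimate 0.333, power about 0.25;
- mean of 6 and 12 months, unadjusted: (2/n)(1 + ρ)/2 = 0.075, SE 0.274, expected estimate 0.5, power about 0.45;
- mean of 6 and 12 months, adjusted for baseline: (2/n)[(1 + ρ)/2 − ρ²] = 0.05, SE 0.224, expected estimate 0.5, power about 0.61.

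All three are optimistic because clinic variance is left out.

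**The interval rule.** This needs no arithmetic beyond setting D.4 (estimation, not testing) against the two sentences in D.5.1 and D.5.2. For scale: at d = 0.5 and ρ = 0.5, about half of simulated trials end with neither the interaction nor the overall difference significant, and so with no interval promised.

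**The case against.** The strongest reply is that the dilution depends on conditions the protocol does not guarantee.

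- **Baseline may not be free of effect.** Clinics are randomised before any Aim 3 child is enrolled, and the same two clinics run both modules. D.2.1 has the screening module prompt referral to early intervention and audiology after a positive screen. First Steps and audiology are items in the Figure 9 count. A real baseline difference is plausible, and the overall difference would then be diluted by less than a third. This stands. It also means that adjusting for baseline, or forcing a common baseline mean, could remove part of an early effect.
- **Baseline may not be collected.** If D.3.4 Data Collection governs, the response holds only 6 and 12 months and the dilution disappears. The D.5.2 model could then not be fitted as written, and there would be no baseline count to adjust for. This stands, and the two sections must be reconciled first.
- **Only one branch is affected.** With a significant interaction, differences are assessed at each time point. This stands. At 0.8 SD and correlation 0.7 the interaction is missed in only 8% of trials.
- **Aim 3 is a declared pilot.** Per-visit means could still inform the next study. That limits the harm, but an estimate for planning is the pilot's main product.

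A reader might also infer that estimates will be shown only when significant, and will therefore be exaggerated. The documents do not support this: the condition in D.5.1 and D.5.2 attaches to the interval, and neither section says that point estimates are withheld. Nor may a reader conclude that every Aim 3 result is diluted, or that Aim 2 is: the Aim 2 model contains no such averaging, and only the interval sentence applies there.

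**Conclusion.** The point holds in two limited parts.

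First, if a baseline count is collected and the interaction is not significant, the planned Aim 3 primary estimate is one third the baseline difference plus two thirds the mean follow-up difference. The two-thirds factor is algebra under the stated random-intercept model with near-complete data. Reading it as a one-third loss of effect further assumes no baseline gap. How often this branch is reached rests on assumed effect sizes and correlations with clinic variance ignored: about 78-88%, 47-75% and 8-43% of trials at 0.3, 0.5 and 0.8 SD. The pre-test is therefore weak protection for small and moderate effects, and better for large ones.

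Second, the rule that an interval follows only from significance is explicit in D.5.1 and D.5.2 and conflicts with the estimation purpose of Aim 3 in D.4. This part depends on no assumption and stands whether or not baseline is measured.

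**What to change.** 1. Reconcile D.3.4 Data Collection with D.5.2 and state whether the activity count is recorded at baseline.
2. In D.5.2, drop the interaction pre-test. Report the treatment difference at 6 and at 12 months, or their mean, and never average in baseline. If a baseline count is collected, adjust for it as a covariate. Note that baseline follows clinic randomisation and may already reflect the screening module, and for that reason also show the unadjusted follow-up difference.
3. In both D.5.1 and D.5.2, report every treatment estimate with its 95% confidence interval whatever the p-value.

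The cost is wording and slightly more reporting. None of the three steps requires a new measurement: if no baseline count exists, the follow-up differences are reported unadjusted.
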